#### Qualitative interviews.

A sub-set of up to 30 women who complete the risk assessment will be recruited to take part in a semi-structured interview lasting up to one hour and covering their views on the entire pathway. We will also ask for verbal consent from women attending an interview for us to potentially contact them about an optional follow-up interview up to six months after the initial interview to gain more in depth understanding of later aspects of the pathway. This sample size reflects the aim of this element of the study, namely to inform the process evaluation and takes into account feasibility and capacity aspects. We will aim to interview women at different levels of risk and, if possible, women from heterogeneous socio-economic backgrounds.

Women who decline to take part in the study are asked to provide a one sentence description of their main reason not to join (decliner form). Women who agree to take part in the study but decline PGS testing are also asked to provide a one sentence description of their main reason to decline PGS testing. If possible, a sub-set of up to 20 women who decline or do not complete specific aspects of the study, including those who do not complete the risk assessment or decline taking part in the study, will be recruited to take part in a semi-structured interview to shed light on potential barriers for future uptake.

A sub-set of up to 10 GPs from all practices will take part in a semi-structured interview lasting up to 30 minutes to learn about their views on the intervention; their participation in the study; their experience completing the CanRisk training; their thoughts about the CanRisk report used to discuss the risk assessment results with women; and time/costs associated with the implementation of CanRisk.

One practice manager and/or research lead per research site will take part in a semi-structured interview lasting up to 30 minutes to gain more in depth understanding about how the study was implemented in their practice and the time/costs associated with the implementation of CanRisk. Practice managers and research leads who decline the invitation for their practices to join the study were also asked to provide their main reason for declining. These data were collected by the Clinical Research Networks in an online Google form.

For women who decline participation in the study, a participant information sheet and consent form for the interviews is provided following the decliner form. Separate consent will also be taken prior to all other interviews. Interviews will be conducted either face to face or online depending on the feasibility and interviewees’ preferences.

#### Video recording of consultations.

A sub-set of 20 GP appointments will be audio- or video-recorded to reflect on how risk, management options and next steps are discussed in practice as well as time spent on CanRisk appointments. Information about this is included in the breast cancer risk assessment results letter for women at increased risk and those interested in this element of the study are asked to contact the study team once they have made an appointment at their GP surgery. Still, between three and five days after women receive the results letter, the study team will follow up with those who do not get in touch spontaneously to confirm their interest. E-consent from women and healthcare professionals to audio or video record appointments will be sought before the appointment. Continued consent will be checked at the beginning and end of the consultation by the GP.

### Sample size

Based on an uptake of 16% in the only study in the UK that invited women to complete a breast cancer risk assessment [35], we estimate that to recruit 1,000 women we need to invite approximately 5,000 women from across the GP practices.

Based on distributions of known risk factors in the UK, we estimate that approximately 17% (170) of those 1,000 women will be at above population-level risk [1]. This will allow us to estimate:

the proportion of eligible women in each practice who consent to take part in the study with an accuracy of +/- 1.1% (width of the 95% CI) based on an estimate of 20%the proportion of eligible women in each practice who consent who complete the risk assessment with an accuracy of +/- 2.5% based on an estimate of 80%the proportion of women who consent who are at moderate or high risk on initial CanRisk assessment in general practice with an accuracy of +/- 2.5% based on an estimate of 17%the proportion of those at moderate or high risk who attend for an appointment with a GP and who are referred to secondary/tertiary care with an accuracy of +/- 5.7% based on an estimate of 80%

Allowing for a 40% loss to follow-up, 1,000 participants will allow us to detect a change in anxiety or worry of 0.5 SD or greater at each time point at p < 0.05 and 90% power in both women at population level risk and in the subgroup identified at moderate or high risk. 1,000 participants will also allow us to detect an estimated increase in the proportion of registered women identified at moderate and high risk through proactive multifactorial risk assessment across all the participating practices compared with the 12 months prior to the study with a 95% confidence interval of +/- 0.005 (5 per 1,000 registered women).

Together with data on the acceptability of the proactive multifactorial breast cancer risk assessment, the following progression criteria will be evaluated to judge whether a subsequent full trial of proactive multifactorial breast cancer risk assessment would be feasible: 16% uptake into the study; 60% response to follow-up questionnaires; 80% of women receiving their breast cancer risk and offered subsequent risk management advice/referral. If any of those criteria are not met, we will use the data from the process evaluation to adapt the approach for subsequent feasibility and/or pilot studies before consider progressing to a subsequent full trial.

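### The invitation number does not follow from its stated basis: at 16% uptake, 5,000 invitations yield about 800 women, not 1,000; the figure of 5,000 silently uses 20%

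*Protocol article*

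**What the plan says.** All the planning figures are in the Sample size section of the protocol article.

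- Basis for the invitation number: "Based on an uptake of 16% in the only study in the UK that invited women to complete a breast cancer risk assessment".
- Conclusion drawn from it: "we estimate that to recruit 1,000 women we need to invite approximately 5,000 women from across the GP practices".
- At-risk group: "we estimate that approximately 17% (170) of those 1,000 women will be at above population-level risk".
- Precision for the consent proportion: "with an accuracy of +/- 1.1% (width of the 95% CI) based on an estimate of 20" per cent.
- Precision for completion, among women "who consent who complete the risk assessment with an accuracy of +/- 2.5% based on an estimate of 80" per cent.
- Progression criteria: "16% uptake into the study; 60% response to follow-up questionnaires", followed by a third criterion of 80% of women receiving their risk and being offered advice or referral.

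The section on study outcomes and measures lists two proportions under uptake, both among women invited: those who consent and those who complete the assessment. The Participant recruitment section lets the number invited depend on practice size, recruitment rate and overall uptake. It closes recruitment on 30 June 2025 or at 1,000 women, whichever comes first.

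**The concern.** The section presents 5,000 invitations as a consequence of 16% uptake, but the two do not agree. Two rates, 16% and 20%, are in use within a few lines, and no sentence connects them. A reader cannot tell which rate the study was planned on, or whether 16% describes women entering the study or women finishing the assessment.

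Two things are at stake. First, if the quoted benchmark is the true consent rate and invitations stay near 5,000, the study falls 20% short of the number on which several precision statements depend. Second, uptake is the first objective and one of three numerical progression criteria. The threshold of 16% is only as clear as its numerator, and the outcomes section offers two. With 16% consent and 80% completion, the study would meet 16% counted by consent but reach only 0.16 × 0.80 = 12.8% counted by completion.

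**Working it through.** **Inputs (all from the Sample size section).** Uptake 16%; invitations about 5,000; recruits 1,000; consent 20%; completion among consenters 80%; moderate or high risk 17%; attendance and referral 80%; loss to follow-up 40%.

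**1. Reproducing the invitation number.** Invitations = recruits / uptake.
- At 16%: 1,000/0.16 = 6,250, which is 25% more than stated.
- At 20%: 1,000/0.20 = 5,000, the stated figure exactly.
- In the other direction: 5,000 × 0.16 = 800, and 5,000 × 0.20 = 1,000.

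**2. Reproducing the consent precision.** Half-width of the 95% CI = 1.96 × √(p(1−p)/n), with n the women invited, pooled over practices.
- p = 0.20, n = 5,000: 1.11%, which matches the stated 1.1%.
- p = 0.16, n = 5,000: 1.02%.
- p = 0.16, n = 6,250: 0.91%.

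The ±1.1% therefore also rests on 20%, not 16%.

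**3. Effect on the other precision figures of 800 recruits instead of 1,000.** The same formula is used on the plan's own denominators.

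| Quantity | Stated | 1,000 recruits | 800 recruits |
|---|---|---|---|
| Completion, p = 0.80 | ±2.5% | ±2.5% | ±2.8% |
| Moderate or high risk, p = 0.17 | ±2.5% | ±2.3% | ±2.6% |
| Women at moderate or high risk | 170 | 170 | 136 |
| Attendance and referral among them, p = 0.80 | ±5.7% | ±6.0% | ±6.7% |

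The last row contains a separate discrepancy. A half-width of 5.7% at 80% needs n = 1.96² × 0.16/0.057² ≈ 189 women, more than the planned 170. Only the step from 6.0% to 6.7% is due to the choice between 16% and 20%.

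**4. Power for a 0.5 SD change after 40% loss, with 800 recruits.** The at-risk subgroup retains 800 × 0.17 × 0.60 ≈ 82 women. A one-sample normal approximation gives Φ(0.5 × √81.6 − 1.96) ≈ 99%. Comparing the at-risk subgroup with the remaining women gives about 98%. Both exceed the stated 90%.

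**5. Is there a reading that reconciles the figures?** 0.20 × 0.80 = 0.16. If 16% means completion among those invited, then 5,000 invitations give 1,000 consenting and 800 assessed. The protocol does not say this. It attaches 16% to recruiting 1,000 women and to entry into the study, and it sets receipt of a risk result as a separate criterion.

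**The case against.** The strongest defence is that 5,000 is an approximate planning figure in a feasibility study with adaptive invitations. The number invited can rise if uptake is low, and lowering the minimum age to 35 may be considered. This stands as a limit on the consequence. A reader might infer that the study will recruit only 800 women; the documents do not support that, although the closing date means that a shortfall remains possible. It does not rescue the calculation, because a 25% gap is too large to be covered by an approximation.

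Several stronger readings are tempting and should not be adopted.

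- *Every figure that depends on 1,000 participants fails.* It does not. The power claim survives, the consent precision depends on the number invited, and the other precisions loosen modestly.
- *Only about 109 at-risk women would remain, with ±7.5%.* This multiplies 800 × 0.17 by a further 80% completion, a step the plan does not apply to its 17%. Setting 7.5% against 5.7% also absorbs the separate discrepancy noted in the working.
- *The planned 170 should itself be 136.* This needs 16% to mean completion and the 17% to apply only to completers. The protocol states neither.
- *A 16% threshold is wrong because planning used 20%.* A progression threshold below the planning rate is not an error in itself.

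On the numerator, the defence can fairly say that uptake into a study most naturally means consent, and that 12.8% is just the product of two thresholds. That is the likelier reading. But the outcomes section lists both consent and completion under uptake, so a clarifying phrase is still needed.

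**Conclusion.** The point holds as an internal inconsistency in the planning figures. The stated basis of 16% does not give 5,000 invitations for 1,000 recruits: it gives 6,250 invitations, or 800 recruits. Both the 5,000 and the ±1.1% rest on an unexplained 20%, and the progression criterion goes back to 16% without saying which of the two listed proportions it counts.

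The practical effect is moderate. The table figures for 800 recruits assume that 16% is the consent rate, that invitations stay near 5,000, that the plan's 80% and 17% apply as stated, and that simple binomial intervals are used. The power statement is not affected. The text should be corrected because the figures cannot stand as written and because the progression criterion should have a fixed numerator before it is judged. The documents do not support a conclusion that the study is undersized for its psychological outcomes.

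**What to change.** Use one rate throughout the Sample size section, in one of two ways.

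- Keep 16% as the consent rate. State about 6,250 invitations for 1,000 recruits, or about 800 recruits from 5,000 invitations, and restate the precision figures accordingly.
- Adopt 20% consent as the planning rate and justify it. If this is what was meant, state the chain explicitly: 20% consent × 80% completion = 16% completion among those invited.

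In either case, say whether the 16% progression criterion counts women who consent or women who complete the assessment, among those invited, on the same basis as the benchmark it comes from. Moving the criterion to completion would make it stricter (20% consent at 80% completion, instead of 16% consent). That is a design choice for the study team, and clarity does not require it.

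The cost is a change of wording and some slightly less favourable stated figures. No extra participants are required. Extra invitations arise only if the team keeps both 16% and the target of 1,000.

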## Aims and objectives

The overall aims of this study are to evaluate the feasibility, acceptability and psychological impact of proactively offering multifactorial breast cancer risk assessment incorporating PGS using CanRisk in general practice, and to collect estimates of outcomes and data on costs and healthcare utilisation. The latter will inform the design of a future trial and a health economic analysis to model the estimated reductions in breast cancer incidence and mortality if proactive breast cancer risk assessment using CanRisk were to be introduced in general practice across the UK.

Specific objectives:

To quantify uptake of proactive multifactorial breast cancer risk assessment using CanRisk in general practice amongst women under 50;To assess the acceptability of all stages of proactive multifactorial breast cancer risk assessment using CanRisk within general practice from the perspective of women, GPs, and staff in General Practice.To compare the number of women identified as at moderate or high risk of breast cancer following proactive multifactorial breast cancer risk assessment with those identified through routine care and the number expected from population-based studies;To quantify the psychological and behavioural impact of proactive multifactorial breast cancer risk assessment using CanRisk in general practice amongst women;To quantify the amount of data collected via the MyCanRisk public-facing data collection tool within a general practice population;To estimate the distribution of breast cancer risk amongst women under age 50 taking up the opportunity for multifactorial risk assessment following proactive invitation and uptake of risk-reducing interventions amongst those at moderate or high risk to inform sample size calculations for the design of a future randomised controlled trial;To estimate differences in uptake of proactive multifactorial breast cancer risk assessment and breast cancer risk distribution of women between general practices to inform the design and sample size calculations for a future cluster-randomised controlled trial;To collect data to enable estimation of the cost of delivering proactive multifactorial breast cancer risk assessment using CanRisk within general practice.

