### Design and setting

The study is a pragmatic multicentre feasibility study taking place in 5–8 GP practices in Cambridgeshire and Peterborough, England, UK. Fig 1 shows the study schedule (SPIRIT).

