#### Participant recruitment.

Eligible women are identified through searches of the electronic health records at General Practices based on the inclusion and exclusion criteria above. To prevent including women who may reach the age of 50 years between the searches being completed and receiving the invitations (see ‘Processes and Interventions’ section below), the search includes women aged 40–48 years. Depending on the population size of each practice, recruitment rate, and overall uptake into the study, either all or a random sample of those women who meet the eligibility criteria are invited to take part in the study. Invitations are staggered in random order. Those women are sent an invitation letter and S3 Participant information sheet by post. A reminder letter is sent by post two to four weeks later to those women who have not completed the consent form.

Women can complete the online written consent form which includes a screening question about breast cancer susceptibility gene already identified within their family. Those answering yes to this screening question are advised to make an appointment to discuss their breast cancer risk with their GP and are not able to continue with the study. After providing online written consent, all participants are asked to complete a short baseline questionnaire (details below) hosted online. On completion of the baseline questionnaire, participants are asked to provide data for a breast cancer risk assessment.

Recruitment opened on the 28^th^ of November 2024 for a duration of 8 months (until the 30^th^ of June 2025) or until 1,000 women have been recruited, whichever happens first.

Participant recruitment and flow through the study is summarised in Fig 2.

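### The ±1.1% and ±2.5% precision stated for each practice is the precision of the whole study; within one practice the intervals are about 2.2 to 2.8 times wider

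*Protocol article*

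**What the plan says.** The Sample size section first gives the study totals: "to recruit 1,000 women we need to invite approximately 5,000 women from across the GP practices". It then lists what this sample will allow. The first bullet is "the proportion of eligible women in each practice who consent to take part in the study with an accuracy of +/- 1.1"%, which the text describes as the width of the 95% CI and bases on an estimate of 20%. The second is "the proportion of eligible women in each practice who consent who complete the risk assessment with an accuracy of +/- 2.5"%, based on an estimate of 80%. The next two bullets, on risk category and on GP attendance and referral, name no practice.

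Design and setting describes a "pragmatic multicentre feasibility study taking place in 5–8 GP practices". Under Participant recruitment, recruitment runs to a fixed date "or until 1,000 women have been recruited, whichever happens first". The seventh specific objective under Aims and objectives is "To estimate differences in uptake of proactive multifactorial breast cancer risk assessment and breast cancer risk distribution of women between general practices", so as to inform the design and sample size of a future cluster-randomised trial.

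**The concern.** The unit named in the two bullets is the single practice, but the only denominators in the section are totals over all practices. If the totals produced the figures, the bullets promise a practice-level precision that the design cannot give.

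The practice level is not incidental here. The seventh objective asks how much uptake differs between practices, and a reader would look to these bullets to see how well the study can answer that. Taken at face value, ±1.1 points per practice implies a half-width of about √2 × 1.11 = 1.6 points for the difference between two practices. With the per-practice numbers the design actually provides, it is about √2 × 2.48 = 3.5 to √2 × 3.14 = 4.4 points. A gap of 3 points would look like a real difference on the first basis and would lie within sampling error on the second.

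**Working it through.** **Inputs.** From Sample size: about 5,000 invited, 1,000 consenting, 20% consent, 80% completion, 95% confidence. From Design and setting: k = 5 to 8 practices. The protocol gives no practice sizes, so equal sizes are assumed. The 16% uptake cited in the same section would imply 1,000/0.16 = 6,250 invitations; the check uses 5,000 and 20% because the precision bullet rests on 20%.

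**Formula.** Half-width = 1.96 × √(p(1−p)/n).

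**Reproducing the stated figures from the study totals.**
- Consent: 1.96 × √(0.2 × 0.8/5,000) = 1.11 points (stated 1.1).
- Completion: 1.96 × √(0.8 × 0.2/1,000) = 2.48 points (stated 2.5).

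The Wilson interval gives essentially the same half-widths (18.91% to 21.13% and 77.41% to 82.36%). Both stated figures therefore come from the pooled totals with independent observations.

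**Per practice, n = 5,000/k invited and 1,000/k consenting.**

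| Practices | Invited each | Consent, ± points | Consenting each | Completion, ± points | Ratio to pooled, √k |
|---|---|---|---|---|---|
| 5 | 1,000 | 2.48 | 200 | 5.54 | 2.24 |
| 6 | 833 | 2.72 | 167 | 6.07 | 2.45 |
| 7 | 714 | 2.93 | 143 | 6.56 | 2.65 |
| 8 | 625 | 3.14 | 125 | 7.01 | 2.83 |

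**Numbers needed to meet the stated precision in every practice**, from n = p(1−p)(1.96/h)²:
- Consent, h = 0.011: 0.16 × (1.96/0.011)² ≈ 5,080 invited per practice, or about 25,400 (5 practices) to 40,600 (8 practices) in total.
- Completion, h = 0.025: 0.16 × (1.96/0.025)² ≈ 983 consenters per practice, or about 4,900 to 7,900 in total.

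**Illustration for the overall figures, on an assumed ICC.** The protocol states none. With design effect 1 + (m−1) × ICC, where m is the number per practice, an ICC of 0.01 gives design effects of 7.24 (8 practices) to 10.99 (5 practices) for consent and 2.24 to 2.99 for completion. The overall half-widths become about 3.0 to 3.7 points and 3.7 to 4.3 points. Over an assumed ICC range of 0.005 to 0.05 they run from 2.3 to 7.9 points and from 3.2 to 8.2 points. The main finding does not depend on these values.

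**The case against.** The best defence is that this is a wording slip. The bullets follow directly on the study totals, the uptake outcome under Study outcomes and measures is defined without a practice level, and the figures are correct as overall binomial precision. No design quantity rests on them: recruitment stops at the target or the end date, and reported intervals will use the observed denominators. All of that stands, and it limits the correction to the text. It does not remove the error, because the practice-level wording appears in two successive bullets, nothing elsewhere corrects it, and a named objective concerns practice-level differences.

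Three stronger readings are tempting, and the document does not support them.

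- A reader might infer that the overall intervals are too narrow for the progression decision. The criterion is 16% uptake, with no confidence limit attached, so no interval enters the decision as written.
- A reader might infer that the overall ±1.1% and ±2.5% are themselves wrong because clustering is ignored. How much they widen depends entirely on an ICC that the document does not give. If the participating practices are treated as fixed strata, the simple interval can be defended. The choice of interval method is commonly left to the analysis plan, which is not shown.
- A reader might make much of the word width. The ± sign already shows that a half-width is meant; a full width of 1.1 points would need about 20,300 women. The label is clerical.

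**Conclusion.** The two bullets are wrong as written: they attach whole-study precision to each practice. Under equal practice sizes, the precision available in one practice is about ±2.5 to 3.1 points for consent and ±5.5 to 7.0 points for completion. With unequal sizes, smaller practices would do worse and larger ones somewhat better. No plausible split rescues the claim, since ±1.1% needs about the whole study's invitations in one practice and ±2.5% needs nearly all its consenters.

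The finding concerns the stated precision and its bearing on the seventh objective. It does not show that the sample size is inadequate for the study's feasibility aims.

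**What to change.** Delete the reference to each practice from both bullets and label ±1.1% and ±2.5% as overall half-widths that assume no variation between practices. Add, as the precision available for the seventh objective, the approximate per-practice half-widths of ±2.5 to 3.1 points (consent) and ±5.5 to 7.0 points (completion), stating that equal practice sizes are assumed.

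Optionally, note that the overall figures widen if uptake or completion varies between practices, and illustrate this over an ICC range labelled as an assumption. Changing width to half-width can be done in the same edit.

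The cost is a few words and a less favourable stated precision at practice level. The recruitment target, number of practices and progression criteria stay as they are, and no new data are needed.

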## Study outcomes and measures

The study aims to generate data on the following outcomes:

Uptake of multifactorial breast cancer risk assessment, including the proportion of those invited who consent and the proportion of those invited who complete the breast cancer risk assessment, with or without the inclusion of the polygenic risk score.Distribution of breast cancer risk, including the proportion of women who consent who are at moderate or high risk on the initial CanRisk assessment in general practice (with or without the PGS) and those at moderate or high-risk following assessment in secondary/tertiary care.Proportion of women at moderate or high risk of breast cancer. The proportion of registered women aged 40–48 years at the start of the study at participating practices who are at moderate or high risk of breast cancer after assessment in secondary/tertiary care will be compared with the proportion of women aged 40–48 years at moderate or high risk of breast cancer after referral to secondary/tertiary care at non-participating practices across Cambridgeshire and Peterborough during the same time period, and also compared with the proportion of registered women aged 40–48 years at participating practices in the 12 months prior to the study.Uptake of risk-reducing interventions, including the proportion of those at moderate or high risk who attend for a GP appointment, are referred to secondary/tertiary care, and take up enhanced screening and/or preventative medication.Completeness of risk factor information collected through MyCanRisk, including the presence of information completed for non-family history risk factors (e.g., height, weight, alcohol, women’s health) and the number of family members included in the pedigree.Change in psychological and behaviour measures (Table 2) following multifactorial breast cancer risk assessment at one month, three months, and six months after receiving the risk estimate.Acceptability of the pathway of proactive multifactorial risk assessment within general practice to women and GPs, including response rates and completion of questionnaires and the willingness for practices to take part.Costs and workload associated with delivery of proactive multifactorial risk assessment.

**Table 2 pone.0336902.t002:** Assessments.

Construct	Baseline	1 month	3 months	6 months

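### The expected number of women at moderate or high risk ignores the plan's own 80% completion rate (about 136, not 170), and the stated +/-5.7% is too narrow at either number

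*Protocol article*

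**What the plan says.** All the planning figures are in the protocol article, Sample size:

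- Recruitment: "we estimate that to recruit 1,000 women we need to invite approximately 5,000 women from across the GP practices".
- Consent: the proportion of eligible women "who consent to take part in the study with an accuracy of +/- 1.1% (width of the 95% CI) based on an estimate of 20" per cent.
- Completion: the proportion of women "who consent who complete the risk assessment with an accuracy of +/- 2.5% based on an estimate of 80" per cent.
- Number at risk: "approximately 17% (170) of those 1,000 women will be at above population-level risk".
- At-risk proportion: "the proportion of women who consent who are at moderate or high risk on initial CanRisk assessment in general practice with an accuracy of +/- 2.5" per cent, at an estimate of 17%.
- Attendance and referral among those at moderate or high risk: the proportion who see a GP and "who are referred to secondary/tertiary care with an accuracy of +/- 5.7% based on an estimate of 80" per cent.

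Two other sections define the quantity being estimated. Study outcomes and measures lists, as part of the risk distribution, "the proportion of women who consent who are at moderate or high risk on the initial CanRisk assessment in general practice". Aims and objectives states the purpose as "To estimate the distribution of breast cancer risk amongst women under age 50 taking up the opportunity for multifactorial risk assessment", in order to inform the sample size of a later randomised trial.

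**The concern.** Consent comes first. The baseline questionnaire and the entry of risk data follow it (Participant recruitment), and the risk group is assigned from the resulting CanRisk estimate (Risk categorisation and returning risk assessment results). A consenting woman who does not complete the assessment has no risk group, so she cannot be advised or referred as at risk. The plan expects one consenter in five to be in that position, yet carries the at-risk count forward as if all 1,000 were classified.

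Two things are at stake. First, the attendance and referral proportion rests on fewer women than stated and will be less precise than promised. Second, the at-risk proportion is meant as an input to a future trial. If its denominator is not fixed, a reader cannot tell whether non-completion is already inside the figure. Someone who took a per-consenter 13.6% and then allowed again for 80% completion would arrive at 0.136 x 0.80 = 10.9%, counting non-completion twice.

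**Working it through.** **Inputs**, all from Sample size: 5,000 invited, 1,000 recruited, 20% consent, 80% completion among consenters, 17% at risk, 80% attending and referred. The confidence level is 95%. The half-width is 1.96 x sqrt(p(1-p)/n).

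**Step 1: reproduce the stated figures.**

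| Quantity | p | n | Half-width | Stated |
|---|---|---|---|---|
| Consent | 0.20 | 5,000 | 1.11% | 1.1% |
| Completion | 0.80 | 1,000 | 2.48% | 2.5% |
| At risk | 0.17 | 1,000 | 2.33% | 2.5% |
| Attend and referred | 0.80 | 170 | 6.01% | 5.7% |

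The first two reproduce, which confirms that the 1,000 are consenters and that the simple normal-approximation formula fits. The last does not. Other interval methods at 80% of 170 give half-widths of 5.98% (Wilson), 6.02% (Agresti-Coull), 5.98% (Jeffreys) and 6.27% (Clopper-Pearson). A half-width of 5.7% needs n = 0.16 x (1.96/0.057)^2, or about 189 women, a number that appears nowhere in the plan.

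**Step 2: apply the plan's completion rate.**

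- Assessed: 0.80 x 1,000 = 800.
- Identified as at moderate or high risk: 0.17 x 800 = 136.
- Shortfall against 170: 34 women, or 34/170 = 20%.
- Consenters needed to identify 170: 170/(0.80 x 0.17) = 1,250.

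**Step 3: precision after the correction.**

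- Attend and referred: 1.96 x sqrt(0.16/136) = 6.72%. With 109 of 136, Wilson gives 6.66% and Clopper-Pearson 7.02%.
- At risk among assessed women: 1.96 x sqrt(0.17 x 0.83/800) = 2.60%.
- At risk per consenter, if non-completers stay in the denominator: 136/1,000 = 13.6%, half-width 2.1%.

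**Step 4: split the gap.** Of the difference between 5.7 and 6.7, about 0.3 point (5.7 to 6.0) is an arithmetic discrepancy at n = 170. About 0.7 point (6.0 to 6.7) comes from non-completion.

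**Step 5: effect on the power statement.** After the plan's 40% loss to follow-up, 136 x 0.6 leaves about 82 at-risk women, against 170 x 0.6 = 102. For a within-group change of 0.5 SD, with the SD of change assumed equal to the reference SD, a one-sample normal approximation gives over 99% power at either number. If baseline and follow-up were uncorrelated, so that the SD of change is larger by sqrt(2), power would be 94.6% at 102 and 89.1% at 82, against the stated 90%.

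**The case against.** The best defence is that 17% describes the underlying risk of the 1,000 recruits, assessed or not. As a statement about the women that may be true. It does not rescue the precision figures: the at-risk item refers to the result of the initial CanRisk assessment, and attendance and referral can be observed only in women identified as at risk. Both 17% per consenter and 80% completion could hold if 0.17/0.80, about 21%, of assessed women were at risk, but the plan does not say so.

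A second defence is that the figures come from one arm of an exact interval. The upper arm is 5.73% for 80% of 170 and 2.47% for 17% of 1,000, close to both printed values. However, the lower arm for the first is 6.81%, so +/-5.7% still misdescribes the interval, and the same convention gives 2.44% for completion, where 2.5% is printed.

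Three objections to stronger readings stand:

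- A reader might infer that the outcome is biased by 3.4 points (13.6% against 17%). That assumes women without an assessment are counted as not at risk. The outcome text does not say how they are handled, and because it is tied to the CanRisk assessment it can be read as restricted to women who have one. A per-consenter yield is also a legitimate quantity in its own right.
- A reader might attribute the whole gap from 5.7 to 6.7 to non-completion. Step 4 shows that part of it is already there at 170.
- A reader might count the +/-2.5% for 17% as a further material error. It is conservative at 1,000 (2.33%) and 0.1 point short at 800 (2.60%).

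It is also fair to say that the outcomes include both the consent and the completion proportions, so the proportion among assessed women can be recovered from the planned data.

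**Conclusion.** Wrong as written, but minor. On the plan's own inputs about 136 women at moderate or high risk will be identified, not 170, and the half-width for attendance and referral is about +/-6.7%, not +/-5.7%. Even with 170 women it would be +/-6.0%. The outcome and the objective name different denominators for the risk distribution. This is a mismatch to resolve, not a demonstrated bias: 13.6% arises only if non-completers are kept in the denominator.

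The result rests on 80% completion and on 17% holding among the women assessed, both taken from the plan. The consequences are limited. None of the progression criteria (16% uptake, 60% questionnaire response, 80% receiving their risk and advice) uses 17%, 170 or +/-5.7%. The 0.5 SD power statement holds if it means within-group change with the SD of change equal to the reference SD, and it falls only marginally below 90% in the at-risk group under zero correlation. Feasibility is not threatened.

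**What to change.** In Sample size, state that about 800 of the 1,000 consenters are expected to complete the assessment and about 136 of them to be at moderate or high risk. Give the precision as about +/-2.6% for 17% of 800 and about +/-6.7% for 80% of 136. If 170 identified women are wanted, the recruitment target would have to be about 1,250 consenters.

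In Study outcomes and measures, define the risk distribution among women with a completed CanRisk assessment, in line with the objective. Report the proportion of all consenters separately, labelled as pathway yield (about 13.6% under the plan's assumptions if non-completers stay in the denominator).

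Unless the target is raised, the cost is wording and arithmetic, and stated precision that is about one point worse for attendance and referral. The denominator should be fixed before the analysis begins.
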